#### **9.2.2.1 Home visits, clinic visits and transport arrangements**

If patients are asked to self-isolate at home, the scheduled follow-up visits during the acute (infectious) phase can take place either in the clinic or at home (home visits are currently standard practice for follow-up of COVID-19 patients in Burkina Faso). The choice will depend on local guidelines in each country and feasibility of transport arrangements and the clinical status of the patient. The overall aim is to minimise the risk of further transmission of COV-SARS-2 and the burden to sick patients self-isolating at home. If patients are requested and able to return to the clinic, special transport arrangement by dedicated vehicles and trained drivers and study staff will be made during the acute infectious phase. In all these circumstances (clinic visits, home visits, transport for staff or participants), strict adherence to personal protection equipment (PPE) and other infection prevention and control (IPC) measures will be followed according to local guidelines in each country to minimize the risk of transmission of SARS-CoV-2 (see also 12.7.3.1, Biohazard containment to limit risks of SARS-CoV-2 transmission, page 65).

#### **9.2.3 Telephone contact Days 2, 4-6, 8-13, 15-27**

Participants who are self-isolating, or have been discharged, will be contacted via mobile phone on the days in between the scheduled visits. Participants will be clinically assessed for signs and symptoms of respiratory distress and will have an in-person assessment of AEs. Support will also be provided with the self-assessment and recording of the daily body temperature, oxygen saturation, pulse and heart rate. As needed, additional contact with the study clinician or staff will be conducted at the request of the participant (e.g., if developing concerning symptoms or an adverse event) or if needed to clarify study procedures or follow-up symptoms.

#### **9.2.4 Close-out visit day 28 Cohort**

In addition to the measurements taken at the other scheduled follow-up visits, a close-out questionnaire will be filled out on day 28 with a brief summary whether the participant completed the study, was lost to follow-up, was (re-)admitted /discharged from/to hospital and when, and survival status.

#### **9.2.5 Close-out visit day 42 nested malaria treatment trial**

In additional malaria-specific close-out visit will take place on day 42 in the patients enrolled in the nested malaria treatment trial to assess the therapeutic response to the antimalarials. The rationale for this additional day-42 visit is based on the standard 6-week duration of follow-up recommended by WHO for treatment efficacy studies of antimalarials.

### 9.2.6 Extended follow-up visits at month 3, 6, and 12

Funding permitting, participants will be asked to return to the clinic for extended follow-up visits 3, 6, and 12 months after enrolment to assess the longevity of the antibody responses to SARS-CoV-2. A sample for malaria RDT, microscopy and PCR will be taken to continue to determine any associations between malaria co-infection and persistence of SARS-CoV-2 immune responses.

### 9.2.7 Participants who develop malaria during the 42 days follow-up period

Participants enrolled in the nested malaria treatment trial who have recurrent malaria detected by microscopy on days 7 to 42 inclusive will be re-treated with the antimalarial from the other arm. Participants without malaria at enrolment who develop clinical malaria during follow-up will be treated with artemether-lumefantrine.

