## 7 INTERVENTIONS

---

If cohort participants are co-infected with malaria, they will be enrolled in the nested malaria treatment trial if they fulfil the eligibility criteria. In each country, participants will be enrolled in one of two treatment arms (see below) and followed weekly for six weeks (42 days). The quarantine and isolation practices and contact tracing will follow the local practices and guidelines in each country.

COVID-19 patient co-infected with malaria will be randomised to receive either a weight-based standard 3-day course of artemether-lumefantrine or a weight-based standard 3-day treatment course of pyronaridine-artesunate. Dosing will follow the standard WHO dosing guidelines.

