#### 7.4.3.2 Concomitant therapy documentation

Participants will be asked about concomitant medications at the screening/baseline evaluation visit. Participants will be counselled to avoid concomitant medications not prescribed by the study clinic, specifically antimalarial drugs. During the study, participants will be asked to complete surveys (Daily Survey and Exit Contact Survey) that include information regarding any medication or vaccine (including over-the-counter or prescription medicines, vitamins, and/or herbal supplements) that the participant receives during the study. At each contact, the Investigator will also question the participant about any medication taken. All concomitant medications taken during the study will be recorded in the appropriate sections of the CRF with indication, dose information, and dates of administration.

All medication used for the management of COVID-19 is permitted, with the exceptions listed under section 7.4.3.3, Prohibited medication, page 38. For COVID-19 participants with malaria who are enrolled in the nested malaria treatment trial, permitted medication includes the use of azithromycin. Other permitted medication includes artesunate or quinine for severe malaria, standard treatments for co-infections (e.g. soil-transmitted helminths, TB, HIV, schistosomiasis, etc.), antibiotics for suspected bacterial infections, haematinics for anaemia, antipyretics/analgesics (e.g. paracetamol, ibuprofen) and treatment for other symptoms as appropriate.

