## 8 DISCONTINUATION/WITHDRAWAL CRITERIA

### 8.1.1 Discontinuation of study treatment

Study treatment for those enrolled in the nested malaria treatment trial will be discontinued for the following reasons:

- Hospitalisation (at the discretion of the inpatient provider, hospitalised participants may continue to receive study treatment if maintained on the originally randomised treatment regimen)
- The requirement for prohibited concomitant medications or other contraindication to study product
- The occurrence of an AE requiring discontinuation of study product, even if not addressed in Section 7.2, page 34
- Request by a participant to terminate study treatment

Participants who stop study product should continue the study participation off study product with continued evaluations as per the Schedule of Activities. The reason for study product discontinuation should be recorded.

Hospitalised participants will be followed through hospitalisation.

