### 9.2.1.3 *Nested malaria treatment trial*

Participants with a positive rapid diagnostic test (HRP2 or pLDH band) or positive microscopy for malaria requiring antimalarial treatment will be potentially eligible for enrolment in the nested malaria treatment trial if they provide informed consent and have mild disease and are able to take oral medication (i.e. have uncomplicated malaria). Patients with RDTs that are positive by HRP2 band only will only be followed if subsequent microscopy confirms the presence of asexual parasitaemia.

Participants will be counselled about the preliminary in vitro data on the activity of the planned treatment arms against malaria and SARS-CoV-2 and equipoise regarding efficacy in humans.

They will then be randomised and receive a box or envelop with their study medication. The first dose on day-0 will be provided as directly observed therapy in the clinic.

Participants will be given some clean water for swallowing the tablets. Participants will then be observed for thirty minutes. In the event of vomiting within thirty minutes of administration after the first dose, a repeat dose should be given. If the repeat dose is vomited, the patient should be given the alternative antimalarial drug from the other arm.

If a dose is missed, it should be taken as soon as realised, and then the recommended regimen continued until the full course of treatment has been completed.

The MOH takes malaria RDTs or malaria microscopy at the same time as the COVID-19 swabbing in symptomatic patients only. Asymptomatic patients are not routinely tested for malaria, and this will, therefore, be conducted as part of the screening study on day 0 or if that was not feasible, later when the results of the COVID-19 test become available and patient return for their results on Day-1. Because the malaria test results are typically known within 20 minutes to 2 hours, treatment will need to be initiated that same day. Eligible patients with both a positive SARS-COV-2 antigen test and a positive malaria test on Day-0 will therefore be invited to enrol in the COVID-19 cohort study and the nested malaria treatment trial that same day (Day-0).

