- treated concomitantly with other drugs that can block potassium channels, such as antiarrhythmics, neuroleptics, certain antimicrobial agents (e.g. macrolides, fluoroquinolones, imidazole and triazole antifungals, pentamidine, saquinavir) and non-sedating antihistamines, cisapride, domperidone or methadone,
- recently treated with medicinal products with long elimination half-life and known to prolong the QTc interval that may still be circulating at the time Pyramax treatment course is commenced (see section 4.8. and 5.1.).

A fall in haemoglobin may occur during treatment. There is very little information on the effect of this in patients with initial haemoglobin levels of less than 8 g/dl. Caution should be exercised in treating patients with a low haemoglobin.

Pyramax should not be used for the treatment of severe malaria, cerebral malaria or other severe manifestations of complicated malaria, including hyperparasitaemia, pulmonary oedema, severe anaemia, renal or hepatic failure. Patients with severe malaria are not candidates for oral therapy.

In patients with acute malaria who present with severe diarrhoea and vomiting, alternative therapy should be considered. If Pyramax is used in these patients, the parasite load should be closely monitored.

Pyramax is a blood schizonticide and for the treatment of *P. vivax* malaria, a radical cure (to destroy the parasite in the liver and thus prevent relapse) is required with a hypnozoitocidal drug such as primaquine.

In the event of proven or suspected recrudescence malaria infections after treatment with Pyramax, patients should be treated with a different blood schizonticide.

Artemisinin compounds should not be used for treatment of malaria in the first trimester of pregnancy if other suitable and effective antimalarials are available (See Section 4.6).

There is no experience in the treatment of mixed *P. vivax* and *P. falciparum* infections. No data are available with Pyramax in the treatment of malaria due to *Plasmodium malariae* or *Plasmodium ovale*.

The safety and effectiveness of Pyramax for the treatment of malaria in patients with HIV/AIDS has not been established. If Pyramax is used in these patients, the parasite load should be closely monitored.

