#### Description of selected adverse reactions

Changes in haematology parameters were generally of similar magnitude in all treatment groups and are expected consequences of malaria infection and treatment. Overall, white cell counts remained constant throughout treatment with falls in neutrophils and compensatory rises in lymphocytes and eosinophils.

Treatment with Pyramax, in keeping with other antimalarials, has caused reductions in haemoglobin of up to 2 g/dL and sometimes more. These generally reached a nadir by Day 3, recovering by Day 28.

In Phase II/III clinical trials that evaluated one single 3-days treatment course, Pyramax treatment was associated with mostly transient ALT elevations, with elevations of  $> 3\times$  upper limit of normal (ULN) and uncommonly,  $> 10\times$  ULN, with early onset peaking between Day 3 and 7 and normalising by Day 28.

In the Phase IIIb longitudinal study Pyramax was administered to patients experiencing single and repeated episodes of malaria and was shown to be similarly well tolerated on repeat administration as for first administration with repeat administration intervals as short as 28 days. The comparator arms of the study, artemether-lumefantrine or artesunate-amodiaquine, or a second study arm of DHA-piperazine, also showed similar tolerability between initial and repeat administration. Where transient ALT elevations occurred, the adverse event profile was slightly higher with repeat administration for both adults and children.

In Episode 1, the percentage of patients with ALT  $> 1.5\times$ ULN and  $\leq 3\times$ ULN for the 4 treatment arms was Pyramax 3.9%, artemether-lumefantrine 2.2%, artesunate-amodiaquine 1.2% and DHA-piperazine 1.6%.

In Episode 2+, the percentage of patients with ALT  $> 1.5\times$ ULN and  $\leq 3\times$ ULN for the 4 treatment arms was Pyramax 5.1%, artemether-lumefantrine 2.2%, artesunate-amodiaquine 2.4% and DHA-piperazine 2.2%.

Cases of syncope and isolated prolonged QTc were uncommonly reported in the available clinical trials for Pyramax. Mean decreases in heart rate were observed in all treatment groups and corresponded to reduction in the fever associated with the malaria infection (see section 4.4. and 5.1.).

In the Phase IIIb longitudinal study, Pyramax compared favourably to the other treatment arms in terms of QTc (Bazett and Fridericia) both on initial or any repeat dose (measured centrally).

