#### *Distribution*

Pyronaridine and its metabolites are extensively distributed into tissues, with highest concentrations achieved in the liver, spleen, adrenal gland, kidney and thyroid gland in the rat. There is evidence that pyronaridine binds to melanin in the eye. In the dog, approximately 6% of a single dose of pyronaridine remained in the liver 24 months after administration. The potential extrapolation to human is not elucidated but the very slow elimination of pyronaridine-related material from the body means that accumulation, with possible hepatotoxicity, cannot be ruled out if pyronaridine is readministered too early.

Pyronaridine preferentially associates with blood cells, exhibiting a whole blood/plasma concentration ratio of approximately 1.5:1. Pyronaridine is highly bound to human serum proteins *in vitro* (92 to 95%). Pyronaridine displays two-compartment pharmacokinetic characteristics with a blood level profile that has a distinct distribution phase.

Artesunate and its metabolites are primarily associated in the rat with tissues involved in absorption and excretion and high levels were also found in the spleen.

Plasma protein binding of artesunate and DHA is moderate (62 to 93%) and albumin is the principal binding protein for DHA in human plasma.

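### The re-treatment rule in Protocol 9.2.7 follows the randomised arm and not the drug received, so an AL-arm participant switched to PA after vomiting would, read literally, get PA again

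*Protocol*

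**What the plan says.** Two rules in the Protocol change a participant's study drug.

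- **Vomiting (9.2.1.3).** A first dose vomited within thirty minutes is repeated. Then: "If the repeat dose is vomited, the patient should be given the alternative antimalarial drug from the other arm".
- **Recurrence (9.2.7).** Trial participants "who have recurrent malaria detected by microscopy on days 7 to 42 inclusive will be re-treated with the antimalarial from the other arm".

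Section 7 describes only two arms, AL and PA. Section 8.1.1 keeps people in follow-up when treatment stops: "Participants who stop study product should continue the study participation off study product with continued evaluations as per the Schedule of Activities". For severe malaria there is a separate route in 7.4.3.2: "Other permitted medication includes artesunate or quinine for severe malaria".

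The Pyramax product text in Appendix VII (16.7.1, SmPC 4.4, tablets and granules) says: "In the event of proven or suspected recrudescence malaria infections after treatment with Pyramax, patients should be treated with a different blood schizonticide". SmPC 5.2 adds that "accumulation, with possible hepatotoxicity, cannot be ruled out if pyronaridine is readministered too early". SmPC 4.8 describes "repeat administration intervals as short as 28 days".

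**The concern.** The evident purpose of 9.2.7 is to change the drug after a recurrence. It does so for everyone who took the drug of their own arm. It fails for a participant who was switched at the first dose, because the rule looks at the allocation and not at what was swallowed.

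For an AL-arm participant already treated with PA, the opposite arm is still PA. The written instruction to site staff then repeats a drug that may just have failed, against the label bound into the same protocol, although AL is at hand. What is at stake is one treatment decision for a rare patient, not the trial's inference.

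**Working it through.** **Step 1. Apply the two rules in sequence.**

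| Arm | Switched after vomiting? | Initial treatment | Drug on recurrence under 9.2.7 |
|---|---|---|---|
| AL | no | AL | PA |
| AL | yes | PA | PA again |
| PA | no | PA | AL |
| PA | yes | AL | AL again |

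The second and fourth rows repeat the drug. The fourth is not a label problem: the appended AL text (16.7.2, SmPC 4.2) accepts, on limited data, a second AL course for new or recrudescent infection. The second row is the issue.

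**Step 2. Look for an exception.** Section 9.2.7 has none for a switched participant. The sections on discontinuation (8.1.1) and on permitted and prohibited medication (7.4.3) do not supply one. Section 8.1.1 stops study treatment for a contraindication in general terms only and names no replacement.

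**Step 3. Is recrudescence in play when the drug is chosen?** The trigger in 9.2.7 is microscopy. Section 10.3.2 separates recrudescence from new infection by genotyping, and 9.2.7 does not wait for that result. Recrudescence can therefore be suspected at the moment of choice, and suspicion is enough for the label sentence to apply.

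**Step 4. Size.** The Protocol states no figure for this sequence, so there is none to reproduce. Inputs:

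- AL arm: 142 / 2 = 71.
- First-dose vomiting: assumed 2%, 5% or 17.5%. The documents give no first-dose rate; 17.5% is the appended AL label's vomiting frequency, not specific to the first dose, and is used as a high value.
- Repeat dose also vomited: assumed 5%, 10% or 20%.
- Recurrence after PA: ITT non-response by day 42 from the Pyramax SmPC 5.1, as a stand-in. At 20 kg or more: 100 − 91.8 = 8.2%. All patients: 100 − 85.6 = 14.4%. Below 20 kg: 100 − 77.3 = 22.7%.

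Expected number = 71 × P(first dose vomited) × P(repeat vomited) × P(recurrence after PA).

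- Low: 71 × 0.02 × 0.05 × 0.082 = 0.006
- Middle: 71 × 0.05 × 0.10 × 0.144 = 0.051
- High: 71 × 0.175 × 0.20 × 0.227 = 0.564

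**Step 5. Sensitivity to the recurrence input.** The same SmPC section gives a PCR-adjusted per-protocol response of 99.6% at day 42, so non-response is 100 − 99.6 = 0.4%.

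- Low: 71 × 0.02 × 0.05 × 0.004 = 0.0003
- Middle: 71 × 0.05 × 0.10 × 0.004 = 0.0014
- High: 71 × 0.175 × 0.20 × 0.004 = 0.010

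**The case against.** The strongest reply is that this is an unwritten corner case. To re-treat someone presupposes that they took the drug of their own arm. A sensible clinician would read the rule as meaning the drug not yet taken, and would find the label sentence in the appendix. That is fair as a forecast of what many clinicians would do, and it limits the harm. It does not mend the text: 9.2.7 and 9.2.1.3 both point to the other arm, and applying both as written gives PA twice.

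It can also be said that 8.1.1 does not squarely cover a switched participant, who is taking the other study drug and has not simply stopped. That is correct, but nothing withdraws such a participant either, and 9.2.7 applies to everyone enrolled in the nested trial.

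Three stronger readings are tempting, and the documents do not support them.

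- **That any repeat of PA breaches the label.** It does not. The label sentence concerns proven or suspected recrudescence. The same product text reports that 434 of 770 patients of 20 kg or more received at least one further treatment, with efficacy maintained and tolerability generally similar, apart from a slightly higher adverse-event profile where transient ALT elevations occurred.
- **That PA is barred within 28 days.** It is not. The early re-administration warning names no interval, follows from animal data, and says that extrapolation to humans is not elucidated. Twenty-eight days is the shortest interval reported, not a stated minimum. The 28-day washout in 6.2.3.2 governs entry, applies equally to AL, and says nothing about re-treatment. The warning is supporting context only.
- **That the trial's results are at risk.** With well under one such participant expected, they are not.

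The objection that the ITT figures overstate recrudescence also stands. The label does not say how new infections and losses enter them, and the Kenyan sites have intense transmission (6.1.1), so new infection is a live alternative. Step 5 shows the effect: the middle figure falls about 36-fold.

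**Conclusion.** The point holds as a minor wording fault with a wrong output in one rare sequence. Section 9.2.7, applied literally after the vomiting switch in 9.2.1.3, gives PA again to an AL-arm participant already treated with PA. Where recrudescence is suspected, that conflicts with the appended Pyramax text.

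The expected number is about 0.05 participants by day 42 (0.006 to 0.56), or about 0.001 (0.0003 to 0.01) if only PCR-adjusted per-protocol failure counts. Both ranges rest on assumed vomiting rates and on label non-response standing in for recurrence. Severe malaria is outside the point because it has its own treatment route. Power, endpoints and analysis are unaffected.

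**What to change.** Reword the first sentence of 9.2.7 so that a trial participant with a microscopy-detected recurrence on days 7 to 42 is *re-treated with the study antimalarial that the participant did not receive as the completed treatment for the initial episode (so a participant switched from AL to PA after vomiting is re-treated with AL)*.

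Treatment of every unswitched participant stays as it is. The switched AL-arm participant returns to AL, the drug vomited at enrolment. This is a real but small drawback: the recurrence rule starts only at day 7, and AL is what 9.2.7 already orders after PA in the PA arm. By the same wording, a PA-arm participant switched to AL would be re-treated with PA, as already happens after AL in the AL arm.

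No minimum interval between PA courses should be added, since the label states none. No unnamed third antimalarial should be added either, because 7.4.3.3 prohibits antimalarials that the protocol does not prescribe.

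The cost is one sentence in a protocol amendment submitted under 12.2.2, which can go with the next one. Visits, sample size and analysis do not change.

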## 10 STUDY ASSESSMENT AND PROCEDURES

---

### 10.1 SCHEDULE OF ACTIVITIES AND SAMPLES

See section 2.2.4, Schedule of activities, page 19 for an overview of all activities and biological samples.

### 10.2 BIOLOGICAL SAMPLES

#### 10.2.1 Mid-nasal swab

We will take two mid-nasal swab sample for research specific molecular detection of SARS-CoV-2 (for later batch analysis, not for patient care). Mid-nasal cavity are less intrusive than nasopharyngeal swabs with less potential for the patient to sneeze, cough, or gag and provide a more comfortable patient experience. Mid-nasal swabs were shown to have a sensitivity of 94% compared to nasopharyngeal swabs.

The nasal swabs will be placed in the plastic tube with transport media, which will be placed into a labelled specimen bag, pre-packaged with an absorbent sheet. One swab will be placed in viral transport media (e.g. DNA/RNA Shield), the other in 0.9% saline, or phosphate-buffered saline, which have been shown to be equivalent for storage of SARS-CoV-2 samples based on validated assays. Previous testing has demonstrated that respiratory viral ribonucleic acid (RNA) is stable in room temperature for up to 1 week. Samples will be stored at -80°C prior to use.

Samples eluted from swabs will be subjected to RNA amplification and tested for SARS-CoV-2 and used for viral invasion assays.

Viral RNA loads will be estimated using quantitative real-time reverse-transcriptase polymerase chain reaction (qRT-PCR) assays which target multiple sites in the SARS-CoV-2 genome, including at least one position each in the Orf1ab and N regions. Validated and standardised quantified plasmid and in vitro transcript RNA controls will be made available to all partner laboratories for use in viral RNA load estimation.

